#### Patient assessments

Patient assessments are being conducted by a trained researcher on practice premises, using standard operating procedures. Baseline assessments are necessary as GP data are non-standardized and will be up to a year old. It is not feasible for researchers to be blinded to allocation, but outcome measures are all objective; an automated sphygmomanometer is used and results of laboratory blood analyses are extracted from GP or local hospital systems. As assessments take place throughout the day, obtaining fasting blood samples is not feasible.

Patient biomedical markers consist of blood pressure, blood lipids, HbA_1c_, BMI, waist circumference, proteinuria, miroalbumiuria and self-reported smoking. In addition to the European Quality of Life-5 Dimensions (EQ-5D) standardized measure of health status developed by the EuroQol Group [35], health status is also being assessed using the short version of World Health Organization’s Quality of Life. We are also assessing satisfaction with services using the Diabetes Treatment Satisfaction Questionnaire (DTSQ) [36] emotional functioning using the Problem Areas in Diabetes (PAID) scale [37]) and continuity of care using a Continuity of Care Questionnaire [38,39]. All these questionnaires are used at both assessments. Additionally, the baseline assessment includes demographic data and prescribed medication. The GP records of patients are also flagged electronically to encourage reporting of death or change of GP.

GPs will be informed of results contributing to national Quality and Outcomes Framework (QOF) indicators which reward GP practices for the provision of ‘quality care’. These include blood pressure, weight/BMI, HbA_1c_, lipids, microalbuminuria and smoking status. This is done because it is possible that patients attending for a research assessment may be less likely to attend for routine clinical assessments.

#### Economic outcome measures

Data on NHS resource use and personal costs to patients are being collected using standard measures for economic analysis [40]. Direct NHS costs include the number of referrals to and attendances at ICCD in the intervention arm and to hospital in the control arm. We are also recording the number of GP, practice nurse, optometrist, podiatrist and dietician consultations, and total hospital attendances, which include both inpatient and outpatient visits. Data are also being collected on prescribed medication and tests linked to diabetes, including diabetic retinopathy tests. For patients who are referred to ICCD, we note the number of contacts with professionals, as well as any group or educational intervention. Direct personal cost data include personal expenditure such as travel costs and indirect costs such as days off sick from work or reduced hours of employment are being collected. These data are obtained at the time of the follow-up assessment.

Impact on health utility will be assessed using the EQ-5D questionnaire [35,41]. Comparing this with costs (directly and indirectly related to patient management) will enable incremental cost-effectiveness of the intervention to be estimated.

#### Qualitative study

Qualitative data focusing on the views and experiences of patients, health professionals and other stakeholders are being collected. Semi-structured exploratory interviews will be undertaken with a sample of approximately 20 patients who have experienced the intervention. This is planned to be a purposive sample, based on responses to the quantitative questionnaires administered at the end of the study. For patients requiring a caregiver, both the patient and caregiver will be interviewed. Where a patient does not speak English, a translator is engaged. A prompt guide was developed through discussion following a literature review and modified after initial piloting. The interviews focus on the patients’ experiences compared to their previous usual care. Participants are free to choose the day, time and venue for the interview. Wherever possible, interviews will be undertaken face-to-face. If necessary, the interview is undertaken by telephone. The choice of face-to-face or telephone follow-up will be decided by the researcher in consultation with the patient, and is dependent on the patient’s own preference.

In addition, semi-structured interviews with health professionals and other stakeholders are being used to explore views in ICCD and experiences of the service. As with the patient interviews, a prompt guide was developed and modified after initial piloting.

### Patients whose preferred language is not English

We are using translated versions of questionnaires if available (for example the EQ-5D). Questionnaires are only completed by people who are fluent in the language of the questionnaire. In circumstances where a patient’s spoken understanding of a language is better than their understanding of written material, we will ask someone to read the questionnaire to them without attempting any translation. All trial literature (that is, consent forms and Patient Information Sheets) is translated. The consent form and patient information sheet have been translated into Bengali, Punjabi, Gujarati and Urdu languages.

### Trial procedures

#### Practice recruitment

The study team first contacted all practices in the relevant PCTs. Practices were sent an invitation letter and short information sheet via the post, and invited to express an interest in participating in the trial. For practices that express an interest, data on current levels of control of patients with T2DM were examined (% patients with HbA_1c_ <7.5, BP145/85 mmHg or less and cholesterol 5 mmol/l or less). These are routinely collected as part of the GP contract [42] and those practices with the highest proportions of poorly controlled patients were invited to join the study.

Practices are recruited on the understanding that they will have access to results on weight, blood pressure, lipids, HbA_1c_ and microalbuminuria from the assessments of patients belonging to their practice. Blood and urine samples are sent to the laboratory for analysis and results sent to practices in the usual way. Research staff record the patient’s blood pressure and weight in the patient’s electronic health records, subject to prior permission from the practice.

#### Practice randomization

Practices recruited to the study were randomized to an intervention or control arm, stratified by practice size and PCT to achieve similar numbers in each arm of the trial. Practices in the intervention arm have access to ICCD service. The study design anticipated that up to 30% of patients in any practice might be eligible for referral to ICCD. Those practices randomized to usual care are issued with local guidelines and continue to manage their patients (including hospital referrals) in the usual way.

Randomization, stratified by area and GP practice size, was undertaken independently of the trial team by Warwick Clinical Trials Unit.

#### Patient recruitment

All patients with poorly controlled T2DM were approached by a letter from their GP enclosing the study information sheet and reply slip. Once the reply slip was received by the research team, patients were written to or telephoned, as appropriate, to explain the aims of the study and arrange an assessment appointment, at which time written consent was obtained by a researcher. An appointment confirmation letter and further copy of the patient information sheet was sent to the patient by post. The aim was to recruit a total of 2,000 patients from 51 practices, with each recruiting approximately 40 patients with poorly controlled T2DM who would be suitable for referral for ICCD support. In a similar study in Denmark 94% consented [18], but assuming a lower consent rate, as seen in UKADS [30] we expect an average sized participating practice with 150 patients with diabetes to recruit 40 to 100 patients. Those not responding to requests for follow-up attendance were reminded using letters, telephone, email and texting.

To enhance the participation rate, GPs and practice nurses at participating practices have been asked to introduce any eligible patients to the study opportunistically as they consult. The research team also offered evening assessment appointments centrally since evening appointments are not possible at general practices due to earlier closing times. Patient confidentiality is assured at non-practice venues, using a locked secure Case Report Form (CRF) box stored in a secure location. Access to the CRF box is restricted to the trial coordinator and research assessors. Laboratory tests are prepared, sent and received in line with usual hospital protocol. To protect patient confidentiality, the patient’s medical history and medication summary notes are extracted from the practice database by a member of the research team, after informed consent has been obtained from the patient.

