**Methods/Design:**

This two-arm cluster randomized controlled trial (with integral economic evaluation and qualitative study) is set in general practices in three UK Primary Care Trusts. Practices are randomized to one of two groups with patients referred to either an ICCD (intervention) or to hospital care (control).

**Intervention group:** GP practices in the intervention arm have the opportunity to refer patients to an ICCD - a multidisciplinary team led by a specialist nurse and a diabetologist. Patients are reviewed and managed in the ICCD for a short period with a goal of improving diabetes and cardiovascular risk factor control and are then referred back to practice.

or

**Control group:** Standard GP care, with referral to secondary care as required, but no access to ICCD.

Participants are adults aged 18 years or older who have type 2 diabetes that is difficult for their GPs to control. The primary outcome is the proportion of participants reaching three risk factor targets: HbA_1c_ (≤7.0%); blood pressure (<140/80); and cholesterol (<4 mmol/l), at the end of the 18-month intervention period. The main secondary outcomes are the proportion of participants reaching individual risk factor targets and the overall 10-year risks for coronary heart disease(CHD) and stroke assessed by the United Kingdom Prospective Diabetes Study (UKPDS) risk engine. Other secondary outcomes include body mass index and waist circumference, use of medication, reported smoking, emotional adjustment, patient satisfaction and views on continuity, costs and health related quality of life. We aimed to randomize 50 practices and recruit 2,555 patients.

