### Sample size

We initially planned to recruit a total of 5,000 patients from 51 practices (25 in one trial arm, and 26 in the other), with approximately 100 patients being recruited from each practice. Due to losses during follow-up, we expected the final number of patients in each practice to be 72, or approximately 3,700 patients in total.

Estimates for the percentage of patients achieving control in the usual care group are taken from a UK survey [4]. We used HbA_1c_ for our primary sample size calculation as this is the outcome variable for which there is the most robust information on intra-class correlation (ICC). To detect a difference of percentage well-controlled (HbA_1c_ <7.5%) from 50% in the control group to 60% in the intervention group (α = 0.05, Power = 0.8not allowing for clustering, requires a sample size of 408 subjects in each arm. Using an Intra-class correlation (ICC) of 0.047, and with 72 patients in each cluster, the necessary sample size in each arm is 1770, representing a total of 3,540 patients for both arms. This number is also adequate to detect a 10% difference in cholesterol control (from 60% to 70%) and blood pressure control (from 60% to 70%). Estimates of ICC for blood pressure and cholesterol are taken from the UK Asian Diabetes Study (UKADS), a study of care provision for people of South Asian ethnicity with diabetes [30]. Assuming the ICC for our combined primary outcome (adequate control of HbA1C, blood pressure and cholesterol) is 0.05 and achievement is at 20% in the control arm and 30% in the intervention arm, we would need a total of 2,848 patients.

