During the recruitment phase, it became clear that we would fall short of the intended 5,000 patients, and of the expected 72 patients per practice. A revised sample size estimate of 40 patients in each practice after follow up (approximately 2,000 patients in total) was proposed and accepted by the ethics panel. Using the same ICC values as previously, and considering the primary outcome, the necessary sample size in each arm is 1,022, for a total of 2,044 (note that this is the necessary sample size for patients retained at follow-up; the sample size for initial recruitment must therefore be larger, or according to our estimates, at least 2,555). This value is approximately sufficient to give power of 80% to detect a 10% difference for both the combined primary outcome and control of blood pressure. We can restore the power to that of the original protocol, before the changes to sample size were made, by considering the detection of a 12% difference for these measures. For control of HbA_1c_ and cholesterol the power is slightly less than 80%.

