## Discussion

The present study will provide a robust estimate of the effects of introduction of intermediate care clinics for diabetes to support the care of patients in UK primary care, and the costs associated with any improvements in outcomes produced. The ICCD model aims to deliver high quality care through a multidisciplinary, locality-based team, with the added opportunity for developing professional expertise in the community. The results of this trial will be of direct policy relevance to the development of diabetes services in the UK, and will provide clinical commissioning groups with evidence to inform decisions on commissioning services to improve control in T2DM. Diabetes and service reconfiguration are both national research priorities but there is an urgent need to base policy on evidence. Modeling suggests the ICCDs will be cost-effective in reducing complications and consequent hospital admissions, as well as producing societal benefits such as reduced incapacity to work. If results from this short-term evaluation are positive they will provide an initial evidence base for adoption and for longer-term evaluations to assess the benefits predicted from modeling. The qualitative study will help identify factors influencing service uptake and, if the trial finds no significant effect, why efficacy was not demonstrated. Forty-nine practices have been randomized and 1,997 patients recruited to the trial. Follow up finished in October 2011 and the results will be available in late 2012. It is not possible at present to comment on the effectiveness or cost-effectiveness of an ICCD service.

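### The recruitment target is given as 2,000 in one section and at least 2,555 elsewhere; with 1,997 recruited, the stated power for the individual targets no longer applies, although the composite stays near 80%

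*Protocol article*

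**What the plan says.** The revised calculation in the Sample size section starts from patients who remain: "A revised sample size estimate of 40 patients in each practice after follow up (approximately 2,000 patients in total". For the primary outcome it then states that "the necessary sample size in each arm is 1,022, for a total of 2,044", notes that this counts patients retained, and concludes that "the sample size for initial recruitment must therefore be larger, or according to our estimates, at least 2,555". The Methods/Design part of the abstract agrees: "We aimed to randomize 50 practices and recruit 2,555 patients".

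The Patient recruitment section instead says: "The aim was to recruit a total of 2,000 patients from 51 practices, with each recruiting approximately 40 patients".

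The power statement attached to the 2,044 covers the composite and the blood pressure target: "This value is approximately sufficient to give power of 80% to detect a 10% difference for both the combined primary outcome and control of blood". For HbA1c and cholesterol the same paragraph says power is a little below 80%.

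The Discussion reports what was achieved: "Forty-nine practices have been randomized and 1,997 patients recruited to the trial". The power statements are not revisited there.

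**The concern.** The same two figures, 40 per practice and about 2,000, mean retained patients in one section and recruited patients in another. Against the Patient recruitment section, 1,997 looks like a target met. Against the abstract and the Sample size section it is 558 short of 2,555 (22%). It is also 47 below the 2,044 needed at follow-up, before anyone is lost.

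The individual risk factor targets head the list of secondary outcomes. The only power figures a reader has for them belong to 2,044 retained. A null result on HbA1c would be read against nearly 80% power when the achieved sample offers less.

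**Working it through.** **Inputs** (Sample size section unless noted): two-sided 5% level (the sidedness is not stated, but two-sided reproduces the plan's figures); HbA1c 50% v 60%, ICC 0.047; blood pressure and cholesterol 60% v 70%, ICC not given; composite 20% v 30%, ICC 0.05. Recruitment is 1,997 in 49 practices (Discussion).

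**Formulas.** Design effect DE = 1 + (m − 1) × ICC, where m is the number retained per practice. Effective number per arm = (N/2)/DE, entered in the two-proportion power formula. Ranges run from continuity-corrected to uncorrected.

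**1. The plan's original figures reproduce with the continuity correction.**
- HbA1c, unclustered: 408 per arm.
- HbA1c, m = 72: 408 × (1 + 71 × 0.047) = 408 × 4.337 = 1,769.5; stated 1,770.
- Composite, m = 72: 2 × 313 × (1 + 71 × 0.05) = 2 × 313 × 4.55 = 2,848; stated 2,848.

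**2. Loss to follow-up.** The revised plan implies 2,044/2,555 = 0.80 retained, a 20% loss. The original plan recruited about 100 per practice and, in its words, "we expected the final number of patients in each practice to be 72": a 28% loss (26% from its totals, 3,700/5,000).

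**3. Projected retention.** 1,997 × 0.80 = 1,598, so m = 1,598/49 = 32.6. At the original plan's loss, 1,997 × 0.72 = 1,438, so m = 29.3.

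**4. HbA1c, worked at 1,598.** DE = 1 + 31.6 × 0.047 = 2.49. Effective number per arm = 799/2.49, about 321. Power is 69.5% corrected and 72.3% uncorrected.

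**5. Power for a 10-point difference, equal practice sizes.**

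| Outcome | 2,044 retained, m = 40 | 1,598 in 49 practices | 1,438 in 49 practices |
|---|---|---|---|
| HbA1c, ICC 0.047 | 74.8–77.1% | 69.5–72.3% | 67.6–70.5% |
| BP or cholesterol, ICC 0.05 (assumed) | 76.5–78.9% | 71.5–74.3% | 69.6–72.6% |
| BP or cholesterol, ICC 0.044 (assumed) | 80.1–82.1% | 74.9–77.5% | 73.0–75.7% |
| Composite, ICC 0.05 | 84.1–86.1% | 79.6–82.1% | 77.8–80.6% |

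At 20% loss, HbA1c, blood pressure and cholesterol each fall by about 5 points from the 2,044 column.

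**6. Why 0.044–0.05 for blood pressure.** The plan's claim of about 80% for blood pressure at 2,044 holds at an ICC of 0.044 (corrected) or 0.048 (uncorrected). The composite's 0.05 is taken as the upper end.

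**7. The 1,022 per arm.** From 20% v 30%, ICC 0.05 and m = 40, DE = 1 + 39 × 0.05 = 2.95. The requirement is 312.8 × 2.95 = 923 per arm corrected, or 293.15 × 2.95 = 865 uncorrected. The stated 1,022 is higher than either, which is why the composite keeps its power when the sample falls short.

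**The case against.** **The loss in power is modest, and on secondary outcomes.** This stands. HbA1c power was already 75–77% at the planned size, so the protocol's description was roughly fair there. The change is about 5 points at 20% loss and about 7 at 28%.

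**The retained numbers are not observed.** This stands too. The protocol reports no retention, and the 28% belongs to the superseded plan. A different loss estimate in a revised plan is not itself an error; 20% is the current figure.

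**Blood pressure and cholesterol rest on an ICC that is not given.** Correct. At an ICC of 0.03, power at 1,598 would be 83.5–85.3%. But it would then have been 88–90% at 2,044, which conflicts with the protocol's own wording. The two outcomes may also have different ICCs, since the protocol describes their power differently for the same 60% v 70%. Only the HbA1c result rests wholly on stated inputs.

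**The main analysis includes all recruited patients, with last observation carried forward.** This does not remove the point. At a full 1,997, HbA1c power is 73.2–75.7%. A baseline value carried forward adds no information about the effect at 18 months.

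**Stronger readings that the document does not support.** A reader might infer that the primary outcome is underpowered. On these numbers it is not: it stays at 78–82%. A reader might also take the 40 to 100 patients mentioned under Patient recruitment as evidence of unequal practice sizes that would lower power further. That range is the expected yield of one average-sized practice under uncertain consent. The protocol gives no measure of spread between practices, so no such penalty can be computed from it.

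**Conclusion.** The contradiction is real and lies in current text: the Patient recruitment section uses retained-patient numbers as the recruitment target. The number recruited is below the stated retained requirement even with no loss.

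For HbA1c, power is about 70–72% at 20% loss (68–71% at 28%). That compares with 75–77% at 2,044 and a stated value slightly under 80%. For blood pressure and cholesterol it is about 72–77% at 20% loss, conditional on an assumed ICC of 0.044–0.05. The composite remains at about 80%. All figures assume equal practice sizes, 1:1 allocation of 49 practices and projected retention. This is worth correcting because it affects how null results on individual targets are read; it does not undermine the primary analysis.

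**What to change.** - In Patient recruitment, state recruited and retained numbers separately, so that the section agrees with the abstract and the Sample size section: 40 per practice and about 2,000 are retained.
- Restate power for each individual target at 1,997 recruited in 49 practices with the 20% loss, and give the blood pressure and cholesterol ICCs used.
- Recheck the 1,022 per arm, and the 2,044 and 2,555 that follow from it. If the figure was driven by another outcome or a higher power, say so.

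The change is to the text only. No further recruitment or design change is asked for. The cost is that the stated power for HbA1c, and probably for blood pressure and cholesterol, becomes somewhat less favourable.

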### Analysis

#### Statistical analysis

Intention-to-treat (ITT) comparisons of the two groups will be conducted, with the primary dependent variable being the proportion of patients achieving all three clinical targets at 18 months. The main analysis will be based on all patients recruited to the study. As some drop-outs and losses are inevitable, sensitivity style analyses are planned. Missing data imputation will use ‘last observation carried forward’ (LOCF). Secondary analyses will exclude all observations with missing values. Analyses will use a mixed effects logistic regression model, and will adjust for baseline characteristics at both practice and individual level. The former may include practice size and deprivation index, and the latter age, gender, BMI, ethnicity, employment status, educational level and length of time since diagnosis. Characteristics will be included using a forward selection model-building strategy, with only variables significant at the 10% level selected. Odds ratios (OR) will be estimated with 95% confidence intervals, adjusting for potential confounding variables and allowing for the effect of the cluster randomization [43].

Further analysis will examine secondary outcomes (achievement of individual targets for blood pressure, HbA1c and lipids), again adjusting for confounders and allowing for the cluster randomization. In addition, UKPDS 10-year risk scores for CHD and stroke will be analyzed using a linear mixed model.

Tertiary analysis of questionnaire responses will consider longitudinal continuity, flexible continuity, relational continuity and term and boundary continuity following the NCCSDO methodology on ‘continuity of care in type 2 diabetes’ [44]. We will also compare the levels of ICCD use by the intervention practices, and the drop-out rates for all practices.

Finally, all analyses will be re-run with added data from MIQUEST covering all diabetes patients in a practice whether recruited to the trial or not [45]. This will lessen the number of variables available, but otherwise all analyses for primary and secondary endpoints will be repeated.

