Practices recruited to the study are randomized to either usual care or intervention arm, with the latter having access to the new ICCD clinics. In participating practices, patients with T2DM are invited to take part in the trial. Recruited patients in both arms are given a baseline assessment by a study nurse. This includes measurement of HbA_1c_, body mass index (BMI), waist circumference, blood pressure, urine and lipids. Participating patients are asked to attend a follow-up assessment 18 months after their baseline assessments, when the same measurements are repeated. Questionnaires about quality of life, satisfaction with current services, continuity of care and health service use and personal costs are completed at baseline and follow-up. An integral economic evaluation measures costs in both groups, with a comparative assessment of marginal costs and outcomes. To deal with possible selection bias, risk factor control of all patients with T2DM in intervention and control practices will be compared using anonymised GP data. Additionally, a qualitative study is exploring the views of patients, health professionals and other stakeholders using semi-structured interviews.

The overall aim is to conduct a randomized controlled trial to evaluate the effectiveness and cost-effectiveness of community-based intermediate care clinics in the management of T2DM. Specific objectives are to:

1. Compare the following in patients with T2DM registered with practices that have access to ICCD with those that have access only to usual care:

·control of cardiovascular risk factors including glycemic, blood pressure and lipid control, and cardiovascular risk assessed by UKPDS risk engine;

·quality of life;

·satisfaction with services and continuity of care;

·referral patterns and non attendance rates;

·annual cost per patient with diabetes.

2. Estimate the difference in the cost of the resources used by patients in each arm of the trial, and the cost-effectiveness of the ICCD intervention.

3. Explore the views and experiences of patients, health professionals and other stakeholders.

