### Outcome measures

The launch of the trial was phased across participating PCTs. Following baseline assessments, practices were randomized and the clinic launched. Eighteen months later follow-up assessments were begun, ensuring that all patients in the intervention arm had 18 months exposure to the ICCD.

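### The named covariates for the primary model leave out baseline HbA1c, blood pressure and cholesterol; they should be pre-specified and kept outside the forward selection

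*Protocol article*

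**What the plan says.** The Statistical analysis section of the protocol article says that the analyses "will adjust for baseline characteristics at both practice and individual level". For the practice level it says "The former may include practice size and deprivation index"; for the patient level it continues with "the latter age, gender, BMI, ethnicity, employment status, educational level and length of time since diagnosis". The selection rule follows: "Characteristics will be included using a forward selection model-building strategy, with only variables significant at the 10% level selected". No section names baseline HbA1c, blood pressure, cholesterol or baseline target status as a covariate.

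These values are collected. The Background section says "Recruited patients in both arms are given a baseline assessment by a study nurse", and of that assessment, "This includes measurement of HbA_1c_, body mass index (BMI), waist circumference, blood pressure, urine and lipids"; the same measurements are repeated at 18 months. Patient assessments justifies the effort: "Baseline assessments are necessary as GP data are non-standardized and will be up to a year old". The Outcome measures section gives the order of events: "Following baseline assessments, practices were randomized and the clinic launched". The values therefore precede allocation and are valid adjustment covariates.

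**The concern.** The primary outcome is built from HbA1c, blood pressure and total cholesterol at 18 months. A patient's starting values of the same three measures are normally among the best predictors of being at target later. A candidate list that has room for employment status and education but not for these looks like an oversight.

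The design does not make up for it. Randomization is stratified by PCT and practice size, not by level of control, although practice-level control data were examined when practices were invited. With only 49 units randomized, the arms can start at noticeably different levels of control by chance. Without the baseline values in the model, that difference is corrected only as far as the named covariates happen to predict control. Recruitment also ended at 1,997 against the 2,555 wanted, so precision available from data already in hand is worth having.

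**Working it through.** **Inputs from the protocol article.** Two-sided α 0.05 (α is stated; two-sided reproduces the figures), power 0.80, 20% v 30%, ICC 0.05, 72 patients per practice in the original plan (Sample size); 15% at target at baseline (Primary clinical outcome measure); 49 practices and 1,997 patients (Discussion); implied retention 2,044/2,555 = 0.80 (Sample size).

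**1. Reproducing the plan's figure.** For 20% v 30% the two-proportion formula with continuity correction gives 313 per arm. The design effect is 1 + (72 − 1) × 0.05 = 4.55. Then 313 × 4.55 = 1,424 per arm, or 2,848 in total, as stated.

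**2. Chance imbalance at baseline.** Assumption: the ICC of 0.05 also applies at baseline.
- Patients per practice: 1,997/49 = 40.8. Design effect: 1 + 39.8 × 0.05 = 2.99.
- Patients per arm: 1,997/2 = 998.5.
- SE of the between-arm difference: √(2 × 0.15 × 0.85 × 2.99/998.5) = 0.0276, or 2.8 points.
- 95% chance range: ±1.96 × 2.76 = ±5.4 points, a little over half of the 10-point target difference.

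Only part of such an imbalance carries through to 18 months, in proportion to the baseline to follow-up correlation. The documents do not give that correlation.

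**3. Illustrative power.** Retained patients: 1,997 × 0.80 ≈ 1,598, or 799 per arm and 32.6 per practice. Design effect: 1 + 31.6 × 0.05 = 2.58. Let R² be the assumed share of outcome variance explained by the baseline values. The effective number per arm is n = 799/[2.58 × (1 − R²)], and power = Φ[(0.10 − 1.96·s₀)/s₁], with s₀ = √(2 × 0.25 × 0.75/n) and s₁ = √((0.2 × 0.8 + 0.3 × 0.7)/n).

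| R² (assumed) | n per arm | Power |
|---|---|---|
| 0 | 310 | 82% |
| 0.10 | 344 | 86% |
| 0.25 | 413 | 91% |

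This power formula has no continuity correction, unlike the plan's sample sizes. The first row is an unadjusted comparison, not the planned adjusted model.

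**4. Check by simulation.** The set-up was 49 practices of 33 patients, three latent risk factors, and a logistic fit on the three baseline values followed by a t-test on practice-mean residuals, with 600 runs per setting. The baseline to follow-up correlations are assumptions.

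| Correlation (practice, patient) | 20% v 30%: unadjusted → adjusted | 20% v 27.5%: unadjusted → adjusted |
|---|---|---|
| 0.3, 0.3 | 83% → 86% | 61% → 61% |
| 0.8, 0.6 | 81% → 97% | 61% → 81% |

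The direction agrees with step 3. The size depends on correlations that the documents do not supply, and in the weakest setting the gain at the smaller effect is nil.

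**The case against.** The strongest reply is that the list is not closed. It is introduced with wording that makes it indicative, the paragraph also promises adjustment for potential confounders, and this is a condensed article whose analysis plan is not shown. That is right as far as it goes: the article does not exclude the baseline values, and a reader should not infer that it does. But the article does name specific candidates and a selection rule. Even if the baseline values were added as candidates, they would still have to pass the 10% threshold.

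A second reply is that randomization deals with imbalance. A reader might infer that the odds ratio is biased, or that a difference in starting control could not be told apart from an effect. Neither follows. Chance imbalance does not bias a randomized comparison on average, the cluster-adjusted confidence interval allows for it, and the named covariates may absorb some of it. What stands is lost precision and a possible distortion of this one estimate.

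Third, the power figures are soft. R² of 10-25% is assumed, the comparator is unadjusted, and multiplying the design effect by (1 − R²) is a linear-model device. In a logistic model, adjustment mainly moves the estimate to a larger conditional value and does not generally shrink its standard error. All of this stands.

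Nor can the gain be read as 11-33% more patients, from 1/(1 − R²). With 49 practices fixed, the variance is proportional to 0.95/N + 0.05/49. At N = 1,598 this is 0.001615. A 10% cut to 0.001453 needs N = 0.95/(0.001453 − 0.001020) ≈ 2,194, which is about 37% more.

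Finally, the documents do not establish that baseline values are complete. Patient assessments says that blood results are taken from GP or hospital systems, so some may be missing.

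**Conclusion.** The point holds as an avoidable weakness in a stated analysis choice. The baseline values of the outcome's own components are measured before randomization and are absent from the named covariates; the model as written is less efficient than it need be and leaves chance baseline imbalance largely uncorrected. The ±5-point range rests on 15% at target and an ICC of 0.05 at baseline. The rise in power from about 82% to 86-91% rests on an assumed R² of 10-25% against no adjustment; the gain over the planned covariates may be smaller.

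A reader might also infer that the UKPDS risk-score models omit baseline risk. The article says only that a linear mixed model will be used and names no covariates for it, so that would be an argument from silence. It is a recommendation here, not a finding.

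**What to change.** Add a sentence to the analysis section: baseline HbA1c, systolic and diastolic blood pressure and total cholesterol, as continuous variables, are included in the primary model irrespective of significance and outside the forward selection. Adjust each individual-target analysis for its own baseline value. As a recommendation, state also that the UKPDS risk models adjust for baseline risk. Settle this before outcomes are compared by arm.

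The cost is small, since no new data are needed. The odds ratio becomes conditional on these values, which should be said when it is reported; the planned adjusted model already yields a conditional odds ratio. Missing baseline values need a simple stated rule, for example single mean imputation that ignores arm, so that no patient is dropped for want of a covariate.
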